# Comparison of the effects of esketamine, sufentanil, or lidocaine combined with propofol on tussis reflection during upper gastrointestinal endoscopy: study protocol for a randomised, two centre, three-blind, controlled trial

**DOI:** 10.1186/s13063-023-07812-0

**Published:** 2024-01-04

**Keywords:** Upper GI, Tussis reflection, Propofol, Esketamine

## Abstract

**Background:**

Tussis, which increases the incidence of airway spasm, aspiration, nausea, and vomiting, is a common complication faced during upper gastrointestinal (GI) endoscopy. However, sedatives and analgesics exhibit inhibitory actions against airway reflexes to different degrees. Our assumption is a combination of propofol and small doses of sufentanil, esketamine, or lidocaine, especially the combination of propofol and esketamine, might reduce tussis incidence.

**Method:**

The study will be performed as a randomised controlled three-blind, two-centre trial. Patients undergoing upper GI endoscopy, ≥ 18 years old, with American Society of Anesthesiologists (ASA) classification I–III will be randomised to four groups: P group (single administration of propofol), P + S group (administration of propofol and sufentanil in combination), P + K group (administration of propofol and esketamine in combination), and P + L group (administration of propofol and lidocaine in combination) (*N* = 100 per group). The primary endpoints include the frequency of tussis, nausea and vomiting, and/or body movements observed at the insertion of the endoscope into the pharyngeal cavity or within 5 min of endoscope insertion. Secondary outcomes are recovery assessment, patients’ and endoscopists’ satisfaction with the procedure, MMSE scores, MET scores, sleep condition, and the number of sedation-related events. Data on sedation-related events are collected by recording of vital signs. Satisfaction parameters and mental states are collected by means of questionnaires and evaluation scales before and after the procedure and on different following days.

**Discussion:**

Esketamine can reduce tussis occurrence with good tolerability and relax the bronchus and also provides high clearance rates and low possibility of adverse reactions. We aim to demonstrate that the combination of esketamine with propofol for sedation in patients subjected to upper GI procedure is nevertheless superior to only administration of propofol or a combination of propofol with other anaesthetics, such as opioids or lidocaine.

**Trial registration:**

ClinicalTrials.gov. NCT05497492, Registered 09 August 2022.

**Supplementary Information:**

The online version contains supplementary material available at 10.1186/s13063-023-07812-0.

## Introduction

The endoscopic technique is the most widely utilised method for the diagnosis and treatment of upper gastrointestinal (GI) diseases and is vital in clinical cases for the screening and treatment of upper GI tumours. However, without anaesthesia, upper GI endoscopy is painful for patients due to possible side effects, such as nausea, retching, tussis, and dyspnoea, caused by frequent stimulations on the throat resulting from the endoscope during comprehensive and careful observation. This discomfort is highly intense for patients with chronic pharyngitis and a drinking and smoking history. A low tolerance of the patients to general upper GI endoscopy often leads to poor results and low willingness for repeated examination. With the development of recent anaesthetic techniques and increasing demand for comfortable medical services, the promotion and popularisation of endoscopy under anaesthesia has become an inexorable trend; thus, patient discomfort is alleviated to the maximum extent during examination [1].

Tussis, which increases the incidence of airway spasm, aspiration, nausea, and vomiting, is a common complication faced during upper GI endoscopy and a protective cough reflex. The airway epithelium is highly sensitive to mechanical and chemical stimuli. The entrance of the endoscope in the oral cavity induces mechanical stimuli to the respiratory tract, activates the cough receptor in the airway, and triggers tussis by activating cough through n-methyl-d-aspartate (NMDA) receptors [2]. However, sedatives and analgesics exhibit inhibitory actions against airway reflexes to different degrees. To date, propofol has been widely utilised for sedation during endoscopy due to its advantages, such as the rapid onset of action; short action time; widespread inhibitory functions on the central nervous system; strong effects on suppressing the contraction of GI smooth muscles, antagonising vomiting reflex; and reducing cough, body movement, and post-operative headache [3, 4]. By contrast, as a single drug, propofol may confer insufficient sedation, weak inhibition against tussis reflection, and short effective duration, thereby necessitating compensation through extra doses. However, repetitive increases in the dose result in the prolongation of postoperative revival, elevated risks of postoperative respiratory depression and hypoxemia, and prolonged hospital residence for postoperative recovery [5, 6]. A study reported reflex reactions induced by stimulating the throat under only propofol anaesthesia [7], which limited the probability of the single use of propofol in endoscopy. Researchers have reported sound sedative effects, inhibitory actions against throat reflection, and stress reactions achieved by the combined use of propofol and small doses of opioids (sufentanil: 0.05 μg/kg or 2–5 μg), which palliates intraoperative pain and discomfort, reduces the postoperative recovery time [8], and is extensively utilised for painless upper GI endoscopy. However, propofol may result in hypotension, bradycardia, and respiratory depression [9]. Research [10, 11] shows that compared with the combination of opiates/benzodiazepines or the use of propofol alone, propofol is more effective and safer when used in combination with ketamine or opiates (sufentanil) and other adjuvants for procedural sedation/anaesthesia.

Esketamine has irreplaceable advantages in maintaining autonomous respiration and sympathetic nervous system-like characteristics. Compared with the combination of opiates and propofol, the combination of ketamine and propofol is preferable, because the latter may increase the possibility of respiratory depression. Esketamine, the d-enantiomer of ketamine with pharmacological actions similar to ketamine’s actions and twice its action intensity provides high clearance rates and low possibility of adverse reactions, which are dose dependent [12]. Small doses of esketamine (recommended dose = 0. 15 mg/kgp [13]) can reduce tussis occurrence with good tolerability. In addition to its role in antagonising NMDAR (the n-methyl-d-aspartate receptor) widespread in the airway, throat, and lungs, esketamine directly acts on airway smooth muscles to expand bronchi through voltage-dependent L-type calcium channel and thus prevents and represses tussis reflection [14]. However, the sympathomimetic action of esketamine contributes to the transient increase in blood pressure and heart rate, whose superimposition with the endoscope insertion–stimulated sympathetic reflex exerts additional burden on the heart and is detrimental to patients with potential myocardial ischaemia [15]. However, when used in combination with propofol, esketamine can not only abolish the suppressive action of propofol on circulation and breathing but also lead to a decrease in propofol doses; thus, esketamine became increasingly popular in clinics [13]. Considering the previously reported evidence about these complementary effects of esketamine as an adjunct to propofol, the combined use of esketamine and propofol may be a promising approach that could reduce the risk of oversedation of propofol in gastrointestinal endoscopy.

Intravenous administration of lidocaine blocks the Na^+^ channel on the sympathetic cell membrane and inhibits the function of the sympathetic adrenal system, transduction of neural signals, and tracheal mechanical stimulation of the function of mucosal sympathetic receptors to prevent tussis reflection. Considerable studies have validated the efficacy of the intravenous injection of 1–2% lidocaine in anaesthesia during upper GI endoscopy; however, the myocardial depression and high individual risks of anaesthetic toxicity necessitate further explicitness of security in applications.

The best approach to analgesia and sedation during upper GI endoscopy is controversial; thus, the development of an appropriate sedative/analgesic strategy that can influence the examination quality, patient cooperation, and degree of satisfaction towards anaesthesia is imperative. From the preliminary observations of clinical trials, we assumed that compared with single-use of propofol, a combination of propofol and small doses of sufentanil, esketamine, or lidocaine, especially the combination of propofol and esketamine, might reduce tussis incidence. To verify our hypothesis, this study expounded the effects of different drugs combined with propofol on tussis reflection in upper GI endoscopy.

## Methods and analysis

### Study design

This paper presents a prospective, randomised, controlled, three-blind, two-centre study registered in the Chinese Clinical Trial Registration Center. The trial will be conducted at Beijing Friendship Hospital and Beijing Tian Tan Hospital, Capital Medical University, China. We have used the SPIRIT reporting guidelines and completed SPIRIT checklist (Additional file 2). Hence, this study enrolled 400 patients (200 patients per centre) from October 2022 to April 2023. Before the study starts, all the staff took a course so they can explain more clearly to the patients, which helped us to get enough participants. The random sequence generator of STATA MP 14 software generated random numbers and divided them into four groups. Patients will be randomly divided into four groups in the ratio of 1:1:1:1. For each selected patient, the researchers drew an envelope to determine their grouping, but the patients were not informed of the grouping. Except for propofol, clinical researchers injected transparent solution into the syringe in random order in the same bottle containing the code. The researchers who conducted randomisation and blinding procedures did not participate in subsequent studies. Other researchers were not informed about the grouping of research and experimental drugs. To ensure the concealment of the allocation, the randomisation results were sealed until the end of the study. The trial auditing process was conducted by an independent team. Whether a centre underwent a monitoring or auditing visit was determined based on scheduling and availability of the auditor, their proximity to each site, and site convenience. We sometimes scheduled the timing of auditing visits for new research staff or following site initiation visits for a different trial led by the Methods Center to reduce travel-related costs. Auditing was conducted in-person.

### Eligibility criteria

Patients who (1) undergo elective upper GI endoscopy under deep propofol sedation, (2) were ≥ 18 years old, (3) meet the classification I–III of American Society of Anesthesiologists (ASA), and (4) give written informed consent were selected.

### Exclusion criteria

Patients with the following medical history criteria will be excluded from the study: (1) allergic reaction to planned medication; (2) gravis myasthenia; (3) history of psychological problems or psychiatric disease; (4) morbid obesity/obstructive sleep apnoea; (5) acute upper respiratory infections; (6) asthma at acute stage; (7) history of unregulated or malignant hypertension, significant ischemic heart disease, severe arrhythmia; (8) uncontrolled hyperthyroidism; (9) severe cardiac, liver, and kidney dysfunction and coagulation disorders; (10) acute upper GI haemorrhage with shock; (11) severe anaemia; (12) GI obstruction with gastric retention; (13) seizure disorders, long-term history of sedative and analgesic drug use, and history of allergy; and (14) increased intracranial pressure and high intraocular pressure.

### Patient and public involvement

The public or patients will not be involved in the design, conduct, reporting, or dissemination plans of this research.

### Randomisation and blinding

Randomisation will be performed as follows. Based on different study centres (two groups), the patients will be classified into four groups: P group (single administration of propofol), P + S group (administration of propofol and sufentanil in combination), P + K group (administration of propofol and esketamine in combination), and P + L group (administration of propofol and lidocaine in combination) (*N* = 100 per group). The random sequence generator of the STATA MP 14 software generated random numbers and divided them into four groups. Only the nurse (A) who is responsible for preparing the trial drug knows the grouping information automatically generated by a computer. She (A) will generate the allocation sequence. The chief anaesthesiologist (B) will enrol patients and assign participants to interventions. Computer-generated random grouping numbers will be printed and placed in separate sealed envelopes. After meeting a participant who meets the inclusion criteria, the anaesthesiologist will assign the newly recruited participant to a group according to the number provided in the envelope. Both the anaesthesiologists and patients are unaware of the treatment plan. Anaesthetic drugs will be prepared and labelled with numbers by nurses and injected by the anaesthesiologists. The anaesthesiologists will record the physiological characteristics of each patient. In emergencies, the nurses can provide the anaesthesiologists the information of drugs to ensure clinical safety. The designed blinding method is as follows: This study will use the three-blind method to ensure the objective evaluation of results. The preoperative preparation of anaesthetic drugs, anaesthesia implementation for upper GI endoscopy, and PACU (postanaesthesia care unit) clinical data collection and follow-up after the operation will be performed by three medical personnel to ensure that pharmaceutist, operators, recorders, and the patients are blind to group classification. On the day of study, an envelope with the smallest sequential number was opened first and the solutions of medicines were prepared in a syringe by an investigator based on the number appeared on the paper slip. Then, the unlabelled syringes of solutions were handed over to an anaesthesiologist who was performing general anaesthesia and administrating the medicines but was blind to the contents inside of the syringes. Another anaesthesiologist who observed and recorded the data intraoperatively and postoperatively was also blinded to the medication patient had received. All sedation procedures were standardised and performed by the same anaesthesiologist who was blind to the patient groups. PACU (postanaesthesia care unit) clinical data collection and follow-up after the operation were also blinded to the therapeutic regimen. The allocation sequence was not available to any member of the research team until databases had been completed and locked. An agreement from PI will allow unblinding of individual participants on a need-to-know basis and, if necessary, termination of treatment in the event the MSO and investigator determine the participant has had a serious adverse reaction to the study medication. Emergency unblinding can be performed at any time if it is considered necessary by the principal investigator. Participants are issued with “In case of emergency” cards to be carried at all times during the study including an emergency phone number. If the trial or a single subject is prematurely unblinded, the principal investigator will document the reason for unblinding and notify the ethics committee. Unblinding of the project statistician who will analyse the data will occur at the end of the study, after the last participant has been evaluated, all data have been entered and cleaned, and the database has been locked.

### Intervention

Figure 1 presents the study outline. The patients are selected according to their inclusion and exclusion criteria for painless upper GI endoscopy and informed consent. The patients will be divided into the four groups: P group (single administration of propofol), P + S group (administration of propofol and sufentanil in combination), P + K group (administration of propofol and esketamine in combination), and P + L group (administration of propofol and lidocaine in combination) (*N* = 100 per group). Baseline information will be collected and recorded before the operation. Anaesthetic drugs will be prepared by the nurses and anaesthetists on the day of the operation as follows: 0.9% normal saline (20 mL) for the P group, 0.5 μg/mL sufentanil (20 mL) for the P + S group as a mixture, 1.5 mg/mL esketamine (20 mL) for the P + K group, and 10 mg/mL lidocaine (20 mL) for the P + L group. Before entering the operating room, the patients will be given lidocaine defoamer for gargling to open the upper limb vein and 5 mL/min lactate Ringer solution. After entering the room, the patients will wear masks to inhale high-flow oxygen, and their vital signs will be monitored and recorded as Tire. Analgesic drugs (diluted to 20 mL according to different concentrations) prepared by the nurses will be slowly injected into their veins 5 min before examination for 30 s with the dose of millilitre 10% kg of body weight, and then, 1.5 mg/kg propofol will be intravenously administrated. Multiple-dose administration is acceptable according to the state of the patient. The endoscope will be inserted when the eyelash reflex disappeared (sedation depth grade: deep sedation). Blood pressure will be recorded after every 3 min from the beginning of the examination, and HR, SpO_2_, and RR will be recorded simultaneously. The primary outcome was the frequency of tussis, nausea and vomiting, and/or body movements observed at the insertion of the endoscope into the pharyngeal cavity or within 5 min of endoscope insertion. When subclinical respiratory depression (90% ≤ SpO_2_ < 95%) occurred, the jaw-thrust manoeuvre was performed to open the airway. When hypoxia (75% ≤ SpO_2_ < 90% for less than 60 s) occurred, in addition to the jaw-thrust manoeuvre, the oxygen flow rate was increased from 2 to 6 L/min. In case of any abnormalities, notifications should be given, and appropriate doses of propofol should be added until the endoscope exits the teeth pad. During endoscopy, 2–4 mL of propofol should be added under the conditions of extended operation time, accelerated breathing, and elevated blood pressure and heart rate to maintain deep sedation. The patients will be transferred to a recovery room after the operation, and their vital signs will be recorded after every 5 min until the patients met the standard of leaving the hospital (Steward score ≥ 4) before discharge. For each patient, the anaesthesia protocol will be completely decided by an investigator based on their experience and expertise and clinical practice guidelines. The intervention was conducted by experienced health professionals under the supervision of researcher groups. In addition, randomly check was performed to make sure the adherence of the staff to the intervention protocols. There were no concomitant interventions that are prohibited during this trial. There is no compensation or post-trial care for participants.

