### Endpoints

The primary endpoints include the frequency of tussis, nausea and vomiting, and/or body movements observed at the insertion of the endoscope into the pharyngeal cavity or within 5 min of endoscope insertion. Secondary endpoints are as follows: (1) the time of the addition of the first drug, from the end of induction to the addition of the first drug (from the injection of the study medication to the disappearance of eyelash reflex); (2) the time of recovery from anaesthesia, from the end of the operation till the patient left the recovery room (the end of operation to consciousness return); (3) perioperative propofol doses; (4) incidence of perioperative adverse events, including tachycardia, oxygen desaturation (the time of 90% ≤ SpO_2_ < 95% for more than 10 s), breathing inhibition (the time of SpO_2_ < 95% for more than 15 s), bradycardia (< 50 beats per minute or a decrease in HR of 20% or more from baseline), and high and low blood pressure (blood pressure < 30% of the basal blood pressure or systolic blood pressure or blood pressure > 30% of the basal blood pressure); (5) incidence of postoperative adverse events (within 6 months after the operation) including nausea, vomiting, increased secretion, dizziness, over sedation, infection, nightmare, uneasiness, itching, disorientation, insanity, breathing inhibition, diplopia, diarrhoea, intestinal obstruction, urinary retention, gastroesophageal reflux, constipation, shiver, and hallucination; (6) MMSE scores, MET scores, and sleep condition after 0.5 h, 2 h, 4 h, 1 day, 2 days, 3 days, 1 week, 1 month, and 6 months of the operation; (7) pharmacoeconomic outcomes (calculated incremental cost-effectiveness ratio based on cost-effectiveness analyses).

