## Discussion

In recent years, for sedation, propofol combined with an analgesic has replaced its conventionally utilised combination with benzodiazepines and has become the standard for analgo-sedation for upper GI endoscopy with the advantages of improved sedation titration, short recovery time, and good patient tolerance and satisfaction. Esketamine offers the advantage of the minimisation of sedation side effects, making optimal use of the synergy concept while acting as an analgesic. Susanne Eberl et al. reported that the use of esketamine in patients during ERCP resulted in good sedation and analgesia quality [13]. However, some main questions remain unanswered. What are the optimal dose and drug compatibility recommended in clinical use? What is the efficacy of esketamine on tussis inhibition? What is the effectiveness of esketamine in the Chinese population? Can esketamine be well tolerated in actual clinical practice? Esketamine is the first esketamine biosimilar developed in China. Phase III studies in China have shown that esketamine with a shorter recovery and orientation recovery times than esketamine presents potential clinical advantages [16, 17]. Although its pharmacokinetics and safety have been reported preliminarily, the data were only from small-scale studies. Moreover, safety analyses in a clinical setting are limited. Therefore, we selected the RCT (randomised controlled trial) for numerous cases to explore the efficacy and safety of esketamine to obtain highly reliable evidence for the clinical application and risk management of esketamine.

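### The Intervention section fixes the sedation regimen, then leaves it wholly to the investigator and prohibits nothing; separately, two sections give different actions for SpO2 of 75% to below 88%

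*Protocol article*

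**What the plan says.** **Regimen.** The Intervention section of the protocol article defines four arms, the control being "P group (single administration of propofol". Each patient receives one prepared 20 mL syringe (saline, sufentanil, esketamine or lidocaine) dosed by body weight 5 min before the examination, then propofol 1.5 mg/kg. Doses may be repeated according to the patient's state. Propofol is the only drug named for top-ups, 2–4 mL on listed triggers. Randomisation and blinding states: "All sedation procedures were standardised and performed by the same anaesthesiologist who was blind to the patient groups".

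The end of the Intervention section says something else: "For each patient, the anaesthesia protocol will be completely decided by an investigator based on their experience and expertise and clinical practice guidelines". Shortly after comes: "There were no concomitant interventions that are prohibited during this trial". The same paragraph mentions random checks of staff adherence to the intervention protocols.

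**Desaturation.** For SpO2 from 75% to below 90% lasting under 60 s, the Intervention section says that "in addition to the jaw-thrust manoeuvre, the oxygen flow rate was increased from 2 to 6 L/min". Its next sentence adds propofol for any abnormality until the endoscope is out. The Assessments section says that below 88% the endoscope is taken out, 100% oxygen is given by mask and breathing is assisted.

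**The concern.** A regimen cannot be both standardised and wholly at each investigator's discretion. These are affirmative statements that conflict, not detail that a condensed article has left to a fuller document.

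The drugs left unprotected are the randomised ones. Taken literally, the two sentences allow an anaesthesiologist to give sufentanil, (es)ketamine or intravenous lidocaine outside the blinded syringe. If that happened before or at insertion, it would fall ahead of or inside the primary endpoint window (insertion and the following 5 min) and could narrow the difference between arms. If it happened after a cough, it could not undo that event where occurrence is scored, but it could still alter two secondary endpoints: "perioperative propofol doses" and recovery time. The adherence checks also lose their standard if the thing to be adhered to may be decided afresh for each patient.

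The SpO2 text concerns a safety action under deep sedation, where staff need one rule.

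**Working it through.** **1. How specific the fixed regimen is.** Read the syringe volume as 0.1 mL/kg (the text puts it as 10% of body weight, in mL). The concentrations in Intervention then give:
- sufentanil 0.5 µg/mL × 0.1 mL/kg = 0.05 µg/kg
- esketamine 1.5 mg/mL × 0.1 mL/kg = 0.15 mg/kg
- lidocaine 10 mg/mL × 0.1 mL/kg = 1 mg/kg

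The first two equal doses cited in the Introduction, which supports this reading. The regimen is fully specified, so the discretion sentence fills no gap; it overrides.

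**2. The statements side by side.**

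| Question | Text that limits | Text that permits |
|---|---|---|
| Who sets the regimen? | Fixed doses (Intervention); standardised (Randomisation and blinding) | The investigator, completely, per patient (Intervention) |
| May another adjunct be given? | Only by implication: control arm is propofol alone; propofol is the only named top-up | No concomitant intervention is prohibited (Intervention) |

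The limit on adjuncts is implied; the permission is explicit.

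**3. What open-label use could do to one contrast.** Let D be the true difference in event rate between P and P + K. Let c be the share of an arm given an open-label adjunct early enough to matter, and b its absolute reduction in event probability in that arm. Then

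D_obs = D − c_P·b_P + c_K·b_K.

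The document gives no c, no b and no baseline tussis rate. If the two products are equal, nothing changes; if c_K·b_K is the larger, the contrast grows. Size and direction are therefore both open.

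As an illustration only, assume use in P alone (c_K = 0), with b_P = e·D, and read the 15% in Sample size calculation as absolute points. Then D_obs = 15 × (1 − c·e), and the sample needed for the same power rises by 1/(1 − c·e)², with variance taken as unchanged:
- c = 5%, e = 0.5: 15 × 0.975 = 14.6 points; factor 1.05
- c = 10%, e = 1: 15 × 0.90 = 13.5 points; factor 1.23
- c = 20%, e = 1: 15 × 0.80 = 12.0 points; factor 1.56

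Power for 100 per arm, two-sided 0.05, e = 1, by assumed control rate:

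| Control rate | c = 0 | c = 10% | c = 20% |
|---|---|---|---|
| 20% | 0.90 | 0.85 | 0.78 |
| 30% | 0.72 | 0.64 | 0.55 |
| 50% | 0.57 | 0.49 | 0.41 |

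These figures show what the open wording could cost under stated assumptions. They do not estimate what it did cost.

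**4. The SpO2 rules as intervals.** Intervention covers 75% to below 90%, for under 60 s. Assessments covers everything below 88%, with no duration condition. They overlap at 75% to below 88% for under 60 s. There, one section names jaw thrust and 6 L/min oxygen without mentioning removal, and the other requires removal with assisted ventilation. From 88% to below 90% they do not conflict.

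**The case against.** The best defence is that specific text governs general text. The syringe, the induction dose and the top-up drug are all named, the control arm is propofol alone, and adherence is checked. On that reading the discretion sentence covers only titration. This stands as evidence of intent: cross-arm adjunct use is very probably not planned. It does not remove the conflict, because the sentence says the protocol is decided completely and the next rule says nothing is prohibited.

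Three stronger readings are tempting, and the document does not support them.

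- *Extra adjunct would fall mainly in the P arm.* A reader might infer this from the Discussion, which says "propofol combined with an analgesic has replaced its conventionally utilised combination with benzodiazepines and has become the standard for analgo-sedation for upper GI endoscopy", and from the Introduction, which says "propofol may confer insufficient sedation, weak inhibition against tussis reflection, and short effective duration, thereby necessitating compensation through extra doses". But the anaesthesiologist is blind to the syringe, and under 1:1:1:1 allocation three patients in four already have an adjunct, so adding one blindly would usually stack drugs. The Introduction passage points to extra doses of propofol, which is also what the Intervention section prescribes. Greater need in the P arm could still show through clinical response, but nothing says it would be met with anything except propofol.
- *Every comparison with P shrinks by the same proportion.* Use in P lowers each such contrast by the same absolute amount, c_P·b_P. That is a common proportion only if the three adjuncts work equally well and the combination arms receive nothing extra. The trial's own hypothesis is that esketamine does best.
- *The protocol orders propofol for desaturation.* The any-abnormality trigger does not except desaturation, but SpO2 responses are set out separately just before it. This is loose wording rather than an instruction.

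The two SpO2 rules can also be read as cumulative, with removal as a further step below 88%. That is a sensible reading, but neither section states it.

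**Conclusion.** The point holds as a contradiction in the text. The Intervention section conflicts with itself and with Randomisation and blinding, and its two explicit sentences permit open-label use of the randomised adjuncts although the arm definitions imply otherwise. Such use could dilute a primary contrast if early, or distort propofol dose and recovery time if later. The frequency, the arm and the size cannot be derived; the range of 14.6 to 12.0 points for a 15-point difference rests on assumed use of 5% to 20% in the P arm only, at half to full effect, and applies to the one contrast shown.

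The SpO2 mismatch is real for 75% to below 88% lasting under 60 s. It is a matter of patient safety; no effect on an estimate is claimed and no frequency is known.

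Both should be corrected: the conflict is plain, its realised effect is unknown, and the repair is cheap.

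**What to change.** - Limit the discretion sentence to propofol titration and rescue care.
- Replace the no-prohibition sentence with a bar on non-study opioid, (es)ketamine and intravenous lidocaine during the procedure, except as recorded rescue. The lidocaine gargle is unaffected. Record the time and reason of any such use and report all of it by arm.
- State one SpO2 action ladder in which the below-88% step in Assessments governs, and except desaturation from the any-abnormality propofol trigger.

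If enrolment is already over, identify off-regimen adjunct use before unblinding from the drug doses and routes that Assessments says are documented, and report it by arm. Where the records cannot separate rescue from other use, exclude no one on that ground.

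The cost is rewording in two sections and, prospectively, one short record field, since the time and reason of an off-regimen drug are not among the items listed. Recorded rescue would remain allowed, so some dilution stays possible, but it would be visible.
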